### Outcomes

#### Primary outcome

Dressing failure: defined as requirement for initial IJ CVAD dressing to be replaced due to the dressing lifting at the edges at any point during CVAD dwell but prior to scheduled dressing change (scheduled dressing changes are every seven days). The requirement for dressing changes will be determined by clinical staff treating the patient, and the clinical indication for dressing change will be recorded. If a patient’s CVAD is removed prior to seven days with the primary dressing still in situ, the dressing will be considered not to have failed.

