### Participant timeline

Participants are enrolled prior to or within 12 h of their CVAD insertion, and will continue on the study until 48 h after their CVAD is removed. It is anticipated that each CVAD will dwell for an average of 7 days, resulting in an average enrolment time for each participant of 9 days (including CVAD dwell whilst in ICU and on the ward).

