### Sample size

A total of 160 patients will be recruited. At 90% power and a significance level of 0.05, 77 patients per group are required to detect a 25% absolute difference in the primary outcome (control failure 50%, intervention failure 25% [2]). To account for potential attrition, three additional patients per group will be recruited.

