### Statistical methods

#### Statistical methods for outcomes

All randomised patients will be analysed by intention to treat, except for those patients whose CVAD insertion is cancelled/failed or who withdraw consent. Continuous data will be reported as means (standard deviation) or median (interquartile limits), as appropriate. Categorical data will be presented as frequency (percentage). The primary outcome, dressing failure, will be investigated using logistic regression with ‘treatment’ as the main effect. Incidence rates of dressing failure, skin colonisation and CLABSI with 95% confidence intervals will summarise the effectiveness of each intervention, and Poisson regression will be used to test for group differences. Kaplan-Meier survival curves (with log rank Mantel-Cox test) will compare dressing failure over time. Other secondary clinical outcomes will be compared between groups with appropriate parametric or non-parametric techniques. *P* values < 0.05 will be considered significant.

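### The Kaplan-Meier curves have no stated rule for CVAD removal; if removal is censored, the curves will not match the day-7 failure proportion that the primary outcome defines

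*Protocol article*

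**What the plan says.** All references are to the protocol article.

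- **Statistical methods for outcomes**, primary analysis: "The primary outcome, dressing failure, will be investigated using logistic regression with ‘treatment’ as the main effect".
- **Statistical methods for outcomes**, time-to-event analysis: "Kaplan-Meier survival curves (with log rank Mantel-Cox test) will compare dressing failure over time". Neither censoring nor competing events are mentioned.
- **Primary outcome**, on early removal: if the CVAD is "removed prior to seven days with the primary dressing still in situ, the dressing will be considered not to have failed". The horizon comes from the same section: "scheduled dressing changes are every seven days". Death is not mentioned there.
- **Participant timeline**: "It is anticipated that each CVAD will dwell for an average of 7 days". No median, spread or share removed before day 7 is given.
- **Eligibility criteria**: patients must be expected to need the device for at least 72 h.
- **Sample size**: "At 90% power and a significance level of 0.05, 77 patients per group are required", based on "control failure 50%, intervention failure 25" per cent.

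**The concern.** Once the CVAD is out, or the patient has died, the initial dressing can no longer fail. These are competing events, not incomplete follow-up. The primary outcome treats early removal in that way: the patient stays in the denominator as a non-failure. A conventional Kaplan-Meier analysis would censor the patient at removal and let those still at risk stand in for them. The two analyses then estimate different quantities:

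- the primary proportion is the share of patients whose initial dressing actually fails within 7 days;
- the censored curve is the share that would fail if every CVAD stayed in.

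At stake is one endpoint reported with two different day-7 failure rates, the higher one on the figure that readers look at first. With a mean dwell equal to the 7-day horizon, early removal will be frequent enough for the gap to show.

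**Working it through.** **1. The plan's own figure.** Two-sided 0.05, 90% power, 50% v 25%, pooled variance, no continuity correction:

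n = [1.960 × √(2 × 0.375 × 0.625) + 1.2816 × √(0.25 + 0.1875)]² / 0.25² = (1.342 + 0.848)² / 0.0625 ≈ 76.7, rounded up to 77 per group.

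The stated 77 reproduces. It is based on the binary outcome and does not depend on the Kaplan-Meier analysis.

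**2. Set-up for the curves.** From the article: day-7 failure of 50% and 25% under the primary rule, horizon 7 days, mean dwell 7 days. Assumed: a constant dressing-failure hazard h per day, removal independent of failure, time counted from insertion, and a dwell distribution with survivor function G(t).

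- Primary proportion (removal counts as not failed): F(7) = ∫₀⁷ h·e^(−ht)·G(t) dt
- Curve with removal censored: 1 − KM(7) = 1 − e^(−7h)
- Share removed before day 7 with an unfailed dressing: 1 − F(7) − e^(−7h)·G(7)

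For each dwell shape, h is solved so that F(7) is 0.50 (control) or 0.25 (intervention).

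**3. Two shapes in full.**

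*Dwell = 3 days plus an exponential of mean 4* (respects 72 h): F(7) = 1 − e^(−3h) + e^(−3h)·[h/(h + 0.25)]·[1 − e^(−4(h + 0.25))].
- Control, h = 0.1285: 0.320 + 0.180 = 0.500. Curve: 1 − e^(−0.8995) = 0.593.
- Intervention, h = 0.0526: 0.146 + 0.104 = 0.250. Curve: 1 − e^(−0.368) = 0.308.
- Removed unfailed, with G(7) = e^(−1) = 0.368: control 1 − 0.50 − 0.407 × 0.368 = 35%; intervention 1 − 0.25 − 0.692 × 0.368 = 50%; about 42% overall.

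*Exponential dwell, mean 7*: F(7) = [h/(h + 1/7)]·[1 − e^(−7(h + 1/7))].
- Control, h = 0.1804: 0.558 × 0.896 = 0.500. Curve: 0.717.
- Intervention, h = 0.0684: 0.324 × 0.772 = 0.250. Curve: 0.380.
- Removed unfailed: 40% and 52%, about 46% overall.
- This shape puts 1 − e^(−3/7) = 35% of removals before 72 h, so it fits the entry criterion poorly and serves only as an outer bound.

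**4. All shapes tried (mean 7 days).**

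| Dwell shape | CVAD dwell under 7 days | Curve at day 7, control v intervention | Removed unfailed, both arms |
|---|---|---|---|
| Normal, SD 2 | 50% | 54.7% v 27.8% | 33% |
| Gamma, CV 0.3 | 54% | 54.9% v 28.0% | 36% |
| Gamma, CV 0.5 | 57% | 58.9% v 30.4% | 38% |
| Log-normal, sigma 0.5 | 60% | 58.9% v 30.4% | 40% |
| 3 days + exponential mean 4 | 63% | 59.3% v 30.8% | 42% |
| Gamma, CV 0.7 | 59% | 63.6% v 33.2% | 41% |
| Log-normal, sigma 0.8 | 66% | 66.1% v 34.9% | 45% |
| Exponential | 63% | 71.7% v 38.0% | 46% |

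The first five rows put fewer than 10% of removals before 72 h; the last three put 21%, 26% and 35% there. In every row the censored curve ends above 50% v 25%. The gap between arms widens too: 59.3 − 30.8 = 28.5 points in the 3-day-plus-exponential case, against 25.

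**5. The test.** In a simulation with 80 per group, exponential dwell and removal independent of arm and of failure (2,000 runs), the log-rank test with removal censored rejected 5.0% of the time under equal hazards. With 50% v 25%, its power was 95.9%, against 92.3% with removed patients held event-free to day 7 and 91.4% for the chi-square test.

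**The case against.** The strongest reply is that the article never says that removal is censored. That is right. Censoring is inferred from the usual convention, and the rule may stand in an analysis plan that is not shown. The only handling rule in the article is the one in the primary outcome; if it were carried over, with removed patients held event-free to day 7, the curve would end at the primary proportions. A reader might infer that the Kaplan-Meier plan contradicts the primary outcome. The text does not support that: without a stated rule there are not two conflicting statements. What remains is that the article names a method whose default use gives a different quantity.

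A reader might also infer that most CVADs come out before day 7, or that most patients are affected. The article gives only a mean; a symmetric dwell puts 50% before day 7. Only removal with an unfailed dressing competes, and that share stays below half overall in every shape tried.

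It can further be said that the censored curve is a legitimate estimate of failure while the device stays in, and that the log-rank test is then sound. Both hold if removal is independent of dressing risk. The curve overstates failure only when it is read as the actual probability of failure, which is the natural reading next to the primary proportion. The Introduction attributes device failure partly to inadequate dressing, which gives some reason to question independence, but the article offers no data on it.

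Finally, the primary outcome is assigned to logistic regression, so it is clear which analysis governs if results diverge.

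**Conclusion.** The point holds for a supporting analysis. The article names Kaplan-Meier curves without a rule for removal or death; under the usual convention their day-7 value will exceed the proportion that the primary outcome defines. For dwell shapes compatible with the 72 h criterion the excess is about 5 to 9 points in control and 3 to 6 in intervention (55-59% v 28-31% against 50% v 25%). The outer bound, exponential dwell, gives 22 and 13 points. Roughly 40-45% of patients would be removed with an unfailed dressing under the more skewed shapes, and about a third if dwell is symmetric.

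The direction does not depend on the dwell shape; the size does. It rests on assumed dwell distributions, a constant failure hazard and independent removal. The primary logistic analysis and the 77 per group are unaffected. Nothing here shows the log-rank test to be invalid.

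**What to change.** Replace the Kaplan-Meier curves with cumulative incidence curves (Aalen-Johansen) to day 7 for failure of the initial dressing. Treat CVAD removal with that dressing in situ, and death, as competing events. State the rule for death explicitly, since the primary outcome does not mention it. With complete follow-up to day 7 or to a competing event, and every other non-failure ending of the initial dressing handled the same way, the curve's day-7 value equals the primary proportion.

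Keep the log-rank test, labelled as a cause-specific comparison of failure while the CVAD is in place. Gray's test is optional: it answers a different question and is not needed for this point.

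The cost is about one sentence and slightly more analysis work in standard software. No new data are needed, because Table 1 already collects dressing-change times, the time and reason of CVAD removal, and date and time of death. The displayed failure curve will be lower than a censored Kaplan-Meier curve.

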#### Secondary outcomes

All-cause CVAD failure: a composite of failure resulting in CVAD removal. Includes pain, infiltration/extravasation, blockage/occlusion (with or without leakage), fracture, thrombosis, dislodgement (complete or partial), or haematomaIndividual types of CVAD failure resulting in CVAD removal [pain, infiltration/extravasation, blockage/occlusion (with or without leakage), fracture, thrombosis, or dislodgement (complete or partial)]‘Central line associated bloodstream infection’ defined as per the National Healthcare and Safety Network (NHSN) [20]‘Primary bloodstream infection’ defined as per the NHSN [20]‘Local infection’ as defined by the Centres for Disease Control and Prevention (CDC)/NHSN ‘Arterial or venous infection’ criteria [21]Loss of dressing integrity not requiring dressing change (i.e. lifting at edges with/without reinforcement required) assessed for all dressings per patientDressing dwell time (from dressing application to removal in days) assessed for all dressings per patientPremature dressing removal (before seven days from dressing application; all dressings per patient)Number of dressing changes (from first application to last removal; all dressings per patient)Device dwell-time (time from CVAD insertion to removal in hours)Serious adverse events (i.e. mortality, CLABSI, MARSI)Adverse skin events relating to MARSI (e.g. pain, itch, erythema, skin stripping, blister, skin tear, irritant contact dermatitis, maceration, folliculitis or infection) [22]Cost (cost and number of products used, cost of treating complications, staff time for device insertion), as informed by standard diagnosis related groups (DRGs), staff time estimates to apply and remove dressings and product costs.Staff and patient satisfaction on dressing application and removal (0 = not at all satisfied to 10 = completely satisfied) assessed at initial application, all dressing changes and final removal for all dressing changes per patient.Skin colonization, measured both descriptively (i.e. organism) and quantitatively (i.e. colony forming units)

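### The premature-removal outcome counts dressings that come off with the catheter, unlike the primary-outcome rule, so it largely tracks CVAD removal and dilutes any adhesion effect

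*Protocol article*

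**What the plan says.** All references are to the protocol article.

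- **Secondary outcomes.** Premature removal is removal of a dressing less than seven days after its application, taken over every dressing the patient has. No reason for removal is required and no exception is given.
- **Primary outcome.** Only the first dressing counts, and CVAD removal is dealt with explicitly: if the CVAD is out before day 7 "with the primary dressing still in situ, the dressing will be considered not to have failed". The same section says that "scheduled dressing changes are every seven days".
- **Participant timeline.** "It is anticipated that each CVAD will dwell for an average of 7 days".
- **Statistical methods for outcomes.** Logistic regression is named for the primary outcome, Poisson regression for certain incidence rates, and Kaplan-Meier with log-rank for dressing failure over time. Premature removal falls under the remainder: "Other secondary clinical outcomes will be compared between groups with appropriate parametric or non-parametric techniques".
- **Table 1.** Dates, times and reasons are recorded for dressing changes and for CVAD removal.

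**The concern.** Take an intact first dressing that comes off on day 5 because the CVAD is no longer needed. The primary outcome scores it as not failed. The secondary outcome scores the same dressing as premature.

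This is the usual case. A dressing still in place at seven days is due for a scheduled change, so the last dressing normally comes off with the CVAD before reaching its own day 7. The exceptions are an exact coincidence and a scheduled change made late. Every dressing on a CVAD that dwells under seven days is premature, in either arm.

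At stake is the meaning of one secondary outcome that bears on the first objective, fewer dressing changes. As defined, it mixes early replacement, which the adhesive could change, with the end of CVAD use, which is a treatment decision.

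**Working it through.** **Inputs from the article.** Control failure 50%, intervention failure 25%, 90% power, significance level 0.05, 77 per group (Sample size); change every 7 days (Primary outcome); mean CVAD dwell 7 days (Participant timeline). **Assumed, because not given:** the shape of the dwell distribution, the failure hazard over time, and variation between patients.

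**1. The plan's own figure.** With a two-sided test and pooled variance, n = [1.96√(2 × 0.375 × 0.625) + 1.2816√(0.25 + 0.1875)]² / 0.25² = (1.3419 + 0.8477)² / 0.0625 = 76.7, so 77. It reproduces and is not in question.

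**2. Decomposition.** Each dressing ends in one of three ways: replaced early, changed on schedule at day 7, or removed with the CVAD. Unless a scheduled change is late, only the second is not premature, so

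share premature = share replaced early + share removed with the CVAD.

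Every patient contributes one dressing of the last kind. Scored per patient as any premature removal, the outcome is therefore 100% in both arms, and simulation gives 100%.

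**3. A case that can be checked by hand.** Let CVAD dwell be exponential with mean 7 days and the failure hazard constant at x per 7 days. Then

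- share reaching the scheduled change: s = e^(−1−x)
- share premature as worded: 1 − s
- share replaced early: [x/(1+x)](1 − s)
- share removed with the CVAD: [1/(1+x)](1 − s)

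*Reading A: 50% and 25% are seven-day risks if the CVAD stays in.* x = −ln(0.50) = 0.693 and −ln(0.75) = 0.288.

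*Reading B: 50% and 25% are the proportions of first dressings scored as failed, with early CVAD removal counted as not failed.* This is closer to how the Sample size section uses them. Solving [x/(1+x)](1 − e^(−1−x)) = 0.50 and 0.25 gives x = 1.263 and 0.479.

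| | A control | A intervention | B control | B intervention |
|---|---|---|---|---|
| Changed on schedule | 18.4% | 27.6% | 10.4% | 22.8% |
| Replaced early | 33.4% | 16.2% | 50.0% | 25.0% |
| Removed with CVAD | 48.2% | 56.2% | 39.6% | 52.2% |
| Premature as worded | 81.6% | 72.4% | 89.6% | 77.2% |

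The difference between arms as worded is 9.2 points (A) or 12.4 points (B). For early replacement alone it is 17.2 or 25.0 points. The contrast is roughly halved because better adhesion means fewer dressings per patient, so the final dressing is a larger share: up 8.0 points in A (17.2 − 8.0 = 9.2) and 12.6 in B (25.0 − 12.6 = 12.4). The final dressings pull against the effect.

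**4. Other distributions, by simulation.**

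- Reading A, exponential or gamma dwell (shape 4 or 16), gamma frailty variance 0 or 1: 81–86% v 72–77% as worded; 33–35% v 16–17% replaced early. Final dressings are 59% (control) and 78% (intervention) of all removals called premature.
- Reading B, gamma dwell (shape 4, minimum 1 day), frailty variance 0 or 1: 88–90% v 78–79% as worded; 42–51% v 20–23% replaced early. With 80 per arm and a patient-clustered test, power is about 77–82% as worded and 99% for early replacement.

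Under the shape-4 gamma, about 56% of CVADs dwell under seven days, and all their dressings are premature.

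**The case against.** **The two outcomes need not share a rule.** They have different names, and a secondary outcome may be broader than the primary. That is fair as far as it goes: the primary is limited to lifting edges and the first dressing, and premature removal may properly include replacement for other reasons. It does not explain why removal with the CVAD should count, since that says nothing about the dressing and happens to nearly everyone.

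**The effect is not lost.** Power of 77–82% as worded is not a blind outcome, and adhesion is also seen in the primary outcome, the failure rates, the Kaplan-Meier curves, loss of integrity and the number of changes. Both points stand. The definition dilutes the effect but does not hide it, and the trial does not depend on this outcome. The percentages also depend on assumed distributions, although the direction of the distortion held in every setting tried.

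**A stronger reading that a reader might infer.** Several outcomes are recorded repeatedly within a patient; satisfaction, for example, is "assessed at initial application, all dressing changes and final removal for all dressing changes per patient". One might conclude that the plan tests dressings as independent records and that its p-values are wrong. The article does not support that. Its sentence on other secondary outcomes asks for appropriate techniques, names no test, does not make the dressing the unit of analysis, and rules out neither a patient effect nor a per-patient summary. Scoring all dressings does not settle the unit either, since the same phrase is attached to a single count per patient: "Number of dressing changes (from first application to last removal; all dressings per patient". Such detail is commonly left to a full protocol or analysis plan, and neither is shown.

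Nor is the direction of error fixed if independence were assumed. In null simulations with 80 per arm and frailty variance from 0 to 2, a nominal 5% test on dressings rejected 2.3% to 12.2% of the time for dwell time and 3.4% to 17.5% for dressing failure. For two or three scores per patient and a correlation of 0.05 to 0.5, the formula 2[1 − Φ(1.96/√(1 + (m − 1)ρ))] gives 5.6% to 16.6%. The article gives neither the correlation nor the number of scores.

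**Conclusion.** The definition of premature dressing removal is a stated rule that gives a distorted result if followed. It calls premature what the primary outcome calls not failed, and it makes nearly every patient's final dressing an event in both arms. That follows from the seven-day schedule alone and needs no distributional assumption beyond scheduled changes being made on time.

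The size does rest on assumptions. About 81–90% v 72–79% of dressings are premature as worded, against about 33–51% v 16–25% when only replacements with the CVAD in place count. In the worked case the absolute contrast is roughly halved.

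One secondary outcome is affected. The primary outcome, its logistic model and the 160 patients are not. Within-patient correlation is a caution for the analysis and not an error in what is written.

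**What to change.** In Secondary outcomes, define premature dressing removal as replacement of a dressing before seven days from its application while the CVAD remains in place. State that a dressing removed with the CVAD is not premature or, if the outcome is analysed as time to replacement, is censored at CVAD removal. Either choice agrees with the primary-outcome rule. Replacement for reasons other than lifting edges can still count, which keeps the outcome distinct from the primary.

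Alongside this, it would help to say that outcomes with several records per patient are analysed by a per-patient summary, by GEE, or with a patient random effect. For premature removal the definition must be corrected first: a per-patient indicator under the present wording would be about 100% in both arms.

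The cost is a few words, settled before the analysis. Table 1 already collects the dates and reasons for dressing changes and for CVAD removal, so no new data, visits or patients are needed. Allowing for within-patient correlation may widen some secondary confidence intervals.

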#### Interim analyses

None planned.

#### Methods for additional analyses

##### Inter-rater reliability

Inter-rater reliability of the daily check site assessment (site complications and evidence of MARSI) will be completed by two research staff at one time point for each of the selected patients using a specific data collection form. Inter-rater reliability will be measured using proportions of specific agreement and by Cohen’s kappa.

##### Cost analysis

Costs between groups will be analysed according to the nursing time taken to conduct dressing changes costed against standard hourly registered nurse wage rates at that site, in addition to cost of resources used as per hospital stores. Costs of treating complications will be based on standard local Diagnosis Related Groups and published estimates.

#### Methods in analysis to handle protocol non-adherence and missing data

Prior to analysis, data will be cleaned and attempts at locating missing data will be made. Missing data that is unable to be found will not be imputed prior to analysis. In addition to intention-to-treat analyses, per protocol analyses will also be completed to address protocol non-adherence.

